## **G. STATISTICAL ANALYSIS**

### **G.1 Overview**

The EAGeR trial is designed as a multi-site randomized double blind clinical trial with two treatment arms: folic acid + aspirin compared to folic acid + placebo. A fixed sample size of 1600 randomized complete subjects is planned. Thus, for planning and statistical power computations we assume that this is the number of subjects who complete the trial and does not include dropouts.

The primary analysis plan is based on an “intention-to-treat” approach comparing the two treatment arms based on the randomized assignment, ignoring later changes in treatment. This analysis is described in Section G.2. The Haifa DCC will perform periodic partial analyses and present interim reports to the DSMB as requested, during Phase II of the trial. It is anticipated that partial analyses will be performed every 6-12 months. The final analysis will be performed upon completion of data collection and editing in Phase III of the trial. Also one full formal interim analysis is planned and the power calculations with considerations for the choice of optimal time for the analysis are given in Section G.3.

In addition to the intention to treat analysis, the Haifa DCC will engage in methodological research with the Project Officer at the NICHD. The focus is on developing statistical methods for clinical prediction models of reproductive outcomes as described in Section G.4, analysis of intermediate endpoints (Section G.5) and evaluating the effect of dropouts and compliance on the study results (Section G.6).

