### G2.2 Intention to treat analysis

The primary analysis of the clinical trial will be “intent to treat” (ITT) analysis based on the total cohort of randomized patients. This approach will be applied to the primary endpoint (live birth) as well as designated secondary endpoints. The difference between the incidence rates of live births for the two treatment groups will be examined by a two-sided test based on the standard Z-score (using the normal approximation to the binomial distribution). The common null hypothesis states that the effect of aspirin on the outcome is null compared to the placebo.

The secondary objectives (as described in Section A) with binary endpoints will be analyzed similarly as comparison of proportions. For binary outcomes such as pregnancy, the time to event may be of interest. In this case, survival analysis methods will be applied with the log-rank test for comparison of the two study treatment groups. For continuous outcome such as birthweight either parametric or non-parametric methods will be used as appropriate. If transformations to approximate a normal distribution are feasible, they will be carried out prior to the parametric analysis. The normality of the data will be examined both graphically using Q-Q plots and by formal tests (Wilks- Shapiro test). For data (either on original or transformed scale) assumed to be normally distributed the comparison of the two treatment groups will be carried out by a t-test. Alternatively if a non-parametric test is required, the Wilcoxon-Mann-Whitney test will be used.

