The following Tables 3 and 4 present results of power calculations for various interim looks plans for the EAGeR trial. These demonstrate the implications of different choices for the number and timing of interim looks. We assume throughout an alpha level of 0.05 and a sample size of 1600 women divided equally to the aspirin and placebo arms of the trial. Previously published studies suggest that for the control group a probability of about 0.70 - 0.80 for live birth given pregnancy ( $P_{preg}$ ) can be expected. Further, the probability of implantation per cycle ( $P_{implant}$ ) was assumed to be constant and in the range between 0.175 and 0.25. Figure 4 shows the probability of live birth (PLB) considering six cycles of menstruation (including both active and passive follow-up):

$$PLB = P_{preg} P_{implant} \sum_{c=1}^6 (1 - P_{implant})^{c-1}$$

**Figure 4.** Probability of live birth versus implantation probability per menstrual cycle

[figure not shown]

Hence a conservative estimate for the live birth rate would be a combination of implantation rate or 17.5% per cycle and a probability of live birth given pregnancy of 70% yielding an estimated value of  $PLB = 0.479$ . The final calculations will be done after the population from which participants are drawn will be identified. A refinement of the calculation can easily incorporate non-fixed probabilities of implantation per cycle

In the following, we consider a range of probabilities for the placebo + folic acid arm of 0.46, 0.48 and 0.50. The effect of the intervention will be measured as the rate ratio (RR) of live birth in the aspirin + folic acid arm compared to placebo + folic acid. We consider effect sizes of 1.15, 1.20 and 1.25. The calculations were preformed using PASS software. Table 3 presents the resulting power for no interim looks and Table 4 shows the power for one or two interim looks for selected outcome probabilities and effect size.

**Table 3.** Power for comparing live birth rates in treatment and placebo groups with no interim looks.

| Live Birth Probability in placebo arm | Live Birth Rate Ratio to be Detected |            |      |
|---------------------------------------|--------------------------------------|------------|------|
|                                       | 1.15                                 | 1.20       | 1.25 |
| 0.46                                  | .77                                  | .96        | .99  |

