| 0.48                                  | .81                                  | .97 | 1.0  |
| 0.50                                  | .84                                  | .98        | 1.0  |

Table 3 shows for example that with 800 women in each treatment arm, we have >80% power to detect effects  $\geq 1.15$  for an assumed overall live birth rate of 0.48 in the placebo group.

Table 4 gives the power for one or two interim looks and the Z-score boundaries, assuming PLB = 0.48 in the placebo arm and a rate ratio of 1.20. For the period 16 – 56 months when live births accumulate, an interim look at 0.45 and 0.6 of the way correspond to 18 and 24 months into the planned recruitment period. In other words, stopping at month 18 of recruitment (24th month of the trial) will “save” the last 6 months of recruitment while by 24 months of recruitment (30th month of the trial) the target sample size should be reached and the stopping will apply to cessation of follow-up and data collection. Alternatively if at this stage aspirin is shown to be effective one could switch the placebo patients to aspirin and continue the follow-up. The decision to stop early will not be made solely on the basis of these statistical tests but will be made by the DSMB taking into account all available information including evaluation of secondary outcomes and ethical issues.

**Table 4.** Power for one or two interim looks assuming PLB = 0.48, RR = 1.2

| Number of interim looks | Time of interim looks | Boundaries  | Power |
|-------------------------|-----------------------|-------------|-------|
| 1                       | 0.45                  | $\pm 2.571$ | 0.490 |
|                         | 1.00                  | $\pm 2.010$ | 0.964 |
| 1                       | 0.60                  | $\pm 2.366$ | 0.718 |
|                         | 1.00                  | $\pm 2.038$ | 0.963 |
| 2                       | 0.45                  | $\pm 2.571$ | 0.490 |
|                         | 0.60                  | $\pm 2.485$ | 0.696 |
|                         | 1.00                  | $\pm 2.050$ | 0.962 |

Thus for example, compared to the naive power of 0.97, one interim look at 0.45 of events accumulation period will results in a very small loss of total power to 0.964

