Even with two interim looks there is very little power loss. Two interim looks at 18 and 24 months into the planned recruitment period yield a high total power of 0.962 and is the proposed plan for the trial.

The high power shown for assessing an effect size of RR =1.2 for the primary outcome of the EAGeR trial indicate that more modest effects could be detected with high probability.

The Lan-DeMets methodology is flexible in that the total number and timing of the interim looks does not need to be specified in advance. Based on results of periodic partial analyses additional looks can be planned and the test boundaries can be adjusted according to the spending function.

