## 1.2 Sensitivity analysis

The following calculations are based on one interim look for futility, and no looks for efficacy. Thus we set  $z_F = z_{1-\alpha/2} = 1.96$ .

We first explore a case where we observe no difference between the two arms at time  $t$ . In this case we observe  $\hat{\delta}(t) = 0$ , and the statistic  $Z(t)$  given by (1.1) is equal zero. Thus, the conditional power at time  $t$  is calculated by plugging  $b(t) = 0$  into (1.6). We analyse this case under two extreme scenarios. In the first scenario we let  $p_0 = 0.48$ , and  $RR = 1.2$  so that  $p_1 = 0.576$ ,  $\delta = 0.096$ , and  $\theta = 3.864$ . The power of the trial is 97%, and we get

the following plot.

[figure not shown]

If we decide to stop the trial for futility if the conditional power value is below 30%, then the probabilities for stopping for futility under  $H_0$ ,  $H_1$ , are given by (1.9)-(1.10) and displayed below.

(a)

[figure not shown]

(b)

[figure not shown]

Now suppose that  $p_0 = 0.4$ , and  $RR = 1.15$  so that  $p_1 = 0.46$ ,  $\delta = 0.06$ , and  $\theta = 2.43$ . The power of the trial is then 68%, and the conditional power values at time  $t$  when no

difference is observed between the two arms is displayed in the plot below.

[figure not shown]

If we decide to stop the trial for futility if the conditional power value is below 30%, then the probabilities for stopping for futility under  $H_0$ , and  $H_1$  are displayed below.

(a)

[figure not shown]

(b)

[figure not shown]

We now explore again the case where we observe no difference between the two arms at time  $t$ , for specific values of  $t$ , as a function of  $p_0$ . In the first scenario we let  $t = 0.2$ ,  $p_0 = 0.4, 0.42, 0.44, 0.46, 0.48$ . The treatment proportions will be calculated as  $p_1 = RR * p_0$ , where  $RR = 1.15$ . This yields  $p_1 = 0.46, 0.483, 0.506, 0.529, 0.552$ ,  $\delta = 0.06, 0.063, 0.066, 0.069, 0.072$ , and  $\theta = 2.43, 2.54, 2.65, 2.77, 2.88$ . The power of

the trial is 68%, 72%, 75%, 79%, 82%, with respect to  $p_0$ , and we get the following plot.

[figure not shown]

If we decide to stop the trial for futility if the conditional power value is below 30%, then the probabilities for stopping for futility under  $H_0$ ,  $H_1$ , are given by (1.9)-(1.10) and displayed below.

(a)

[figure not shown]

(b)

[figure not shown]

Now we introduce the same scenario for time  $t = 0.3$ .

[figure not shown]

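### The inference that effects smaller than RR 1.2 would be detected with high probability is not supported: two-look power is about 79–82% at RR 1.15 and 45–48% at RR 1.10, with no dropout reserve

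*Supplement*

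**What the plan says.** The relevant statements are in the latest protocol version and in the separate interim-analysis chapter.

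- **Sample size (G.1).** The target is 1,600 complete subjects. For power, "we assume that this is the number of subjects who complete the trial and does not include dropouts". A complete subject is one who attends at least 90% of scheduled clinic visits (C.1, D.2).
- **Primary test (G2.2).** An intention-to-treat comparison of all randomised women by a "two-sided test based on the standard Z-score (using the normal approximation to the binomial distribution").
- **Power inputs (G.3).** "We assume throughout an alpha level of 0.05 and a sample size of 1600 women divided equally to the aspirin and placebo arms". On the rate ratio, "We consider effect sizes of 1.15, 1.20 and 1.25".
- **Table 3, no interim looks.** At RR 1.15 the power is .77, .81 and .84 for placebo rates of 0.46, 0.48 and 0.50. The text concludes that "with 800 women in each treatment arm, we have >80% power to detect effects" of 1.15 or more at a placebo rate of 0.48.
- **Table 4, with looks.** Computed only for one case, "assuming PLB = 0.48 in the placebo arm and a rate ratio of 1.20". Looks at 0.45 and 0.60 with boundaries 2.571, 2.485 and 2.050 give 0.962, and G.3 names this the proposed plan.
- **The inference.** From the power at RR 1.2, G.3 says the results "indicate that more modest effects could be detected with high probability".
- **Interim-analysis chapter, section 1.2.** At RR 1.15, with placebo rates of 0.40, 0.42, 0.44, 0.46 and 0.48 and no efficacy looks, the power of "the trial is 68%, 72%, 75%, 79%, 82" per cent respectively.

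**The concern.** High power at one effect size says little about smaller ones, because power falls steeply as the effect shrinks. The sentence states a general property of the design without a figure, and the only power computed under the proposed looks is at RR 1.2. The plan's own numbers already show strain at RR 1.15: .77 in Table 3 at a placebo rate of 0.46, and less than 80% in four of the five scenarios in the interim-analysis chapter, all before any efficacy look.

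The power also rests on completers, while the test is on all randomised women. No dropout rate is given, and there is no rule for women whose outcome is unknown.

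What is at stake is how a null result is read. At a placebo rate of 0.48, RR 1.10 means 0.528 against 0.480, or 4.8 more live births per 100 women. A reader relying on the sentence could take a null result as evidence against a benefit of that size.

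**Working it through.** **Inputs.** n = 800 per arm and two-sided alpha 0.05 (G.3); placebo rates p0 from Table 3 and from the interim-analysis chapter; looks and boundaries from Table 4. RR 1.10 and 1.12 are values chosen for this check; the documents do not tabulate them.

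**Formulas.** p1 = RR × p0 and p̄ = (p0 + p1)/2. The drift is θ = (p1 − p0 − c)/√(2p̄(1 − p̄)/n), with c = 1/n = 0.00125 under a continuity correction and c = 0 without. Power with no looks is Φ(θ − 1.96). Power with looks is the chance that a Brownian motion with drift θ crosses the upper boundary at t = 0.45, 0.60 or 1, found by numerical integration.

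**Step 1: reproduce the plan (p0 = 0.48, with correction).**
- RR 1.20: p1 = 0.576 and p̄ = 0.528, so θ = (0.096 − 0.00125)/0.02496 = 3.796. With no looks, Φ(1.836) = 0.967 (Table 3: .97). With two looks the cumulative power is 0.490, 0.695, 0.962 (Table 4: 0.490, 0.696, 0.962).
- RR 1.15: p1 = 0.552 and p̄ = 0.516, so θ = (0.072 − 0.00125)/0.02499 = 2.831. With no looks, Φ(0.871) = 0.808 (Table 3: .81).

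Both tables therefore reproduce, and the continuity-corrected method is the closer match.

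**Step 2: apply the same method to smaller effects.** For RR 1.10, p1 = 0.528 and p̄ = 0.504, so θ = (0.048 − 0.00125)/0.02500 = 1.870.

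Two choices are open, so the check covers both. G2.2 mentions no continuity correction. Table 4's boundaries spend about 0.010 and 0.018 at the two looks, which matches 0.05t² (0.05 × 0.45² = 0.0101; 0.05 × 0.60² = 0.018) and not the O'Brien-Fleming function that G.3 names. Boundaries of that type are 3.144, 2.693 and 1.982.

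Two-look power:

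| p0 | RR | Table 4 bounds, corrected | Table 4 bounds, uncorrected | O'Brien-Fleming type, corrected | O'Brien-Fleming type, uncorrected |
|---|---|---|---|---|---|
| 0.48 | 1.20 | 0.962 | 0.966 | 0.966 | 0.969 |
| 0.48 | 1.15 | 0.792 | 0.806 | 0.805 | 0.818 |
| 0.48 | 1.12 | 0.595 | 0.614 | 0.611 | 0.630 |
| 0.48 | 1.10 | 0.445 | 0.464 | 0.460 | 0.480 |
| 0.50 | 1.15 | 0.826 | 0.839 | 0.838 | 0.850 |
| 0.46 | 1.15 | 0.756 | 0.771 | 0.770 | 0.785 |
| 0.40 | 1.15 | 0.640 | 0.659 | 0.656 | 0.674 |

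An unpooled variance raises the uncorrected entries by about 0.002 at most. The looks cost little: at p0 = 0.48 and RR 1.15, power goes from 0.808 to 0.792 with Table 4's boundaries. G.1 speaks of one formal look where G.3 proposes two. One look at 0.45 gives 0.799 at RR 1.15 and 0.453 at RR 1.10, so the conclusion does not turn on that.

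**Step 3: dropout, as an illustration only.** Assume 5% dropout in each arm, scored as no live birth. The rates become 0.48 × 0.95 = 0.456 and 0.552 × 0.95 = 0.5244. If 1,600 is the randomised total (n = 800), two-look power at RR 1.15 is 0.748–0.778 across the four variants. If 1,600 is the completer total (n = 800/0.95 ≈ 842), it is 0.771–0.798.

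**The case against.** Several objections have force.

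- **RR 1.10 is not the plan's value.** G.3 considers 1.15, 1.20 and 1.25, so an effect smaller than 1.2 may simply mean 1.15, where power is about 80%. Without the correction and with Table 4's boundaries, 90% is reached at about RR 1.171. This stands as far as it goes: the sentence is tolerable at 1.15 and good at 1.17. But it sets no lower limit, and it follows from neither table for anything smaller.
- **The placebo rate is deliberately conservative.** G.3 takes 0.479 from the bottom of both input ranges; the top gives 0.80 × (1 − 0.75⁶) = 0.658. At that rate two-look power is about 0.99 at RR 1.15 and 0.78–0.81 at RR 1.10. The gestational diabetes sub-study (D.11.b) expects 60% successful pregnancies; read as a placebo live-birth rate, that gives about 68% at RR 1.10. This also stands, yet G.3 draws its inference at 0.48, and the interim-analysis chapter goes down to 0.40.
- **The bases are disclosed.** Table 3's title says it has no looks, and G.1 states the completer basis openly. Correct.

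A reader might infer that power at RR 1.15 is below 80% under the proposed plan. The documents do not establish that. At p0 = 0.48 it happens only when the continuity correction and Table 4's printed boundaries are combined, and then by 0.8 points. Nor is the statement of more than 80% power wrong: it cites the no-look table, for which it is correct.

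A reader might also infer a definite loss of power from the intention-to-treat analysis. That cannot be derived. Missing the 90% visit rule is not the same as an unknown outcome, live birth is taken from hospital records (G.2.1), and Amendment 3 plans to contact women who withdrew. If 1,600 is the completer number, the randomised cohort is larger, and power falls only if dropouts are scored as failures or the effect is diluted.

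**Conclusion.** The general inference in G.3 is unsupported by the plan's own method and proposed design. At a placebo rate of 0.48 on 1,600 completers, two-look power is about 79–82% at RR 1.15, 60–63% at RR 1.12 and 45–48% at RR 1.10; the last stays below one half in every variant tried at that rate. At RR 1.15 it is about 0.76–0.79 at a placebo rate of 0.46 and 0.64–0.68 at 0.40.

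These figures hold no reserve for dropout. The mismatch between completers and the randomised cohort is plain in the text, but its cost depends on a dropout rate and a scoring rule that the documents do not give. Under the illustrative 5% scored as no live birth, power at RR 1.15 and placebo 0.48 is roughly 75–80%.

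This is a fault in a stated power claim. Tables 3 and 4 themselves reproduce, and the interim looks cost only about 1.5 points.

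**What to change.** 1. Delete the sentence about smaller effects, or limit it to the effect sizes for which a figure is shown.
2. Tabulate power for the looks and boundaries actually adopted, at RR 1.10, 1.15 and 1.20, over placebo rates of 0.40 to 0.50, with a stated dropout assumption and a stated rule for unknown outcomes in the intention-to-treat analysis.
3. Say whether 1,600 is the number randomised or the number completing.
4. Describe power at RR 1.15 as about 80% at a placebo rate of 0.48, with no dropout reserve.

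The cost is text and a short calculation. No patients are added and neither design nor test changes; the stated figures become slightly less favourable.

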#### *Data and Safety Monitoring Board*

A Data and Safety Monitoring Board (DSMB) will be established to provide independent guidance to the study conduct. The members of the DSMB will include experts in relevant fields, potentially to include endocrinology, fertility, reproductive epidemiology, biostatistics and bioethics. DSMB members are appointed by the Director of the NICHD. The DSMB reports to the NICHD director through the NICHD Project Officer and the DESPR Director. The DSMB is charged with reviewing all interim data for safety and efficacy and for recommending to the Project officer any actions that should be taken to insure the ethical conduct of the trial. Results of all such reviews will be available to the investigators upon completion of the trial and unblinding. Final decisions for study continuation or discontinuation will be made by the NICHD Director. The DSMB will also have to provide periodic reports for submission to site IRB's stating the study continues and other necessary updates.

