### **G.2 Study endpoints and intention to treat analysis**

#### **G.2.1 Study endpoints: operational definition and verification**

Study endpoints will be determined based on self-reports, self-administered pregnancy tests, clinic pregnancy tests, medical record evaluations (including routine pregnancy follow-up, ultrasound) and laboratory tests. Whenever possible, we will verify the endpoints using different sources of information. For example, a report by a woman of a positive pregnancy test will be verified against the laboratory results for urine hCG around the same date of the self-reported pregnancy. Similarly, self-reports of pregnancy loss will be ascertained by medical records (in case of a clinically recognized pregnancy) or by blood and urine tests around the same time point (in cases of early loss <12 weeks' gestation).

Operational definitions for a study outcome events are detailed in Section C.4. The sources of information for study endpoints ascertainment:

- a) Live birth – based on hospital records
- b) hCG detected pregnancy (implantation) – a self-report of a positive home pregnancy test followed by a spot urine test in the clinic and quantitative hCG evaluations in urine and serum specimens.

- c) Early loss of pregnancy (ELP) – hCG pregnancy loss will be defined as a rise of urinary HCG to  $>0.025$  ng/mL for at least 3 consecutive days followed by a decline. The rise and fall of HCG will be evaluated during the 10 days prior to the next menstrual period through day 5 of the next menstrual period. Clinically recognized pregnancy losses will be identified based on self-report followed by confirmation on ultrasound and medical records,
- d) Specific pregnancy outcomes: Cesarean section, preeclampsia, gestational age, preterm birth birthweight [small for gestational age], major neonatal complications or death, and severe post-partum maternal morbidity will be determined based on hospital records and medical chart abstraction.

All events will be reviewed and verified by a central outcome review that will be performed by the NICHD Project Officer and the Principal Investigators at the study clinical sites and the Data Coordinating Center.

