#### **G.7 Implementation of statistical analysis**

Data analysis will be performed on personal computers at the Haifa DCC using SAS, STATA and R software. Questions related to data analysis and methodological issues will be discussed periodically in the weekly staff meetings at the DCC. Interim results will be summarized and presented at the DSMB meetings and discussed with the Project Officer. Holding regular discussions of study analysis is crucially important to ensure that study aims are met and that the interpretation of data is valid. Publication quality summaries of the results of the statistical analyses will be prepared by the Haifa DCC team for interim and final reports, presentations and manuscripts.

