### **Reports and newsletter**

The Haifa DCC will be responsible for preparation and distribution of interim and final reports, quarterly newsletter, presentations and other publications in coordination with

the Project Officer at the NICHD and in collaboration with the study investigators. Reports will include summaries of recruitment and follow-up status, by Clinical Site, graphical and tabular presentations and results of interim statistical analysis. The reports will have clear explanations of the methods used, interpretations and point out questions or problems that need special attention.

Special reports of adverse events occurring during the course of the study will be prepared periodically and submitted to the Project Officer and the DSMB.

The quarterly newsletter will be made available on the study Web-site and contain information on the progress and performance of the clinical centers.

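### G.3 lets the results of partial analyses prompt extra looks, so alpha spending no longer guarantees the 5% level; access to interim results also needs tightening

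*Supplement*

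**What the plan says.** G.3 of the latest protocol adopts Lan-DeMets spending of O'Brien-Fleming type and proposes two interim looks, at 0.45 and 0.60 of the period when live births accumulate (months 16 to 56). It notes that the number and timing of looks need not be fixed beforehand, then adds: "Based on results of periodic partial analyses additional looks can be planned and the test boundaries can be adjusted according to the spending function". On frequency, G.1 says: "It is anticipated that partial analyses will be performed every 6-12 months". These analyses are run by the DCC and go to the DSMB. G.1 counts one formal interim analysis where G.3 proposes two. The separate Interim Analysis chapter at the end of the supplement keeps a spending function and works through a futility look. It does not withdraw or limit the permission in G.3.

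On access, G.7 says: "Interim results will be summarized and presented at the DSMB meetings and discussed with the Project Officer". G.2.1 says: "All events will be reviewed and verified by a central outcome review that will be performed by the NICHD Project Officer", and the same sentence goes on to name the principal investigators at the sites and the DCC. Section F places the Project Officer on the Steering Committee with those investigators and gives that committee the final say on the protocol. On DSMB reviews, section F says: "Results of all such reviews will be available to the investigators upon completion of the trial and unblinding". Section H (Reports and newsletter) has the DCC prepare reports in collaboration with the investigators, and lists among their contents "graphical and tabular presentations and results of interim statistical analysis".

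**The concern.** A spending function fixes how much alpha has been used by time t. Boundaries computed from it keep the total at 5% if the look times are set in advance or changed for outside reasons such as slow accrual or a moved meeting. If a look is added because the difference looks large, the trial is tested selectively where the path happens to be high. The analysis that prompted the look has been charged nothing. Recomputing the boundary afterwards does not repair this.

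The strict 5% claim for the primary endpoint is therefore at stake. So is the trial's answer to a critic who asks whether a look was called because the data had already crossed.

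The access question is related but separate. Someone who has seen results by arm and then helps to classify events, or to change the protocol, can be influenced by them. No passage masks the outcome reviewers to interim results; the masking text in D.5b covers participants and clinical-center staff.

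**Working it through.** **Inputs.** G.3: "We assume throughout an alpha level of 0.05 and a sample size of 1600 women divided equally". G2.2: the primary comparison "will be examined by a two-sided test based on the standard Z-score". G.3 and Table 4: placebo rate 0.48, rate ratio 1.20 (so 0.576), looks at t = 0.45, 0.60 and 1.00, window of months 16 to 56. G.1: partial analyses every 6 to 12 months.

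**Step 1: reproduce Table 4.** The drift is θ = δ√N/(2σ), with δ = 0.096, N = 1600 and σ² = [0.48×0.52 + 0.576×0.424]/2. This gives θ = 3.864, the value in the Interim Analysis chapter. With the printed boundaries 2.571, 2.485 and 2.050, simulation of 2 million paths gives cumulative power 0.509, 0.714 and 0.967 (printed 0.490, 0.696 and 0.962) and total two-sided error 0.050. With look times fixed in advance, the 5% level holds.

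**Step 2: spending function.** The usual two-sided O'Brien-Fleming form is α(t) = 4[1 − Φ(z₁₋α/₄/√t)]. It gives boundaries 3.144, 2.693 and 1.982, which are not those in Table 4. The printed boundaries match α(t) = 0.05t² (2.572, 2.485, 2.047). Equation 1.4 as printed reaches only 0.025 at t = 1, so I used the form that spends 0.05. That mismatch is a separate matter; both functions are shown so that the result does not hinge on it.

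**Step 3: partial-analysis times.** t = (month − 16)/40. Six-monthly from month 22 gives 0.15, 0.30, …, 0.90. Twelve-monthly from month 28 gives 0.30, 0.60, 0.90.

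**Step 4: opportunistic rule (assumed).** The looks at 0.45, 0.60 and 1.00 are kept and charged. At any other partial analysis, a look is declared only if |Z(t)| exceeds c. Here c is the boundary for a look at t following the planned looks already done, spending α(t) minus what they used. Null simulation, 2 million paths (Monte Carlo standard error about 0.0002):

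| Partial analyses | O'Brien-Fleming | 0.05t² |
|---|---|---|
| every 6 months from month 22 | 0.0585 | 0.0605 |
| every 6 months from month 24 | 0.060 | 0.063 |
| every 12 months from month 28 | 0.056 | 0.057 |

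Starting the yearly series at month 24 gives slightly less (0.055 and 0.056). With only the look at 0.45 planned, as the count of one in G.1 would allow, the schedules from months 22 and 28 give 0.058 to 0.066.

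**Step 5: trend rule (assumed).** If |Z| at a partial analysis exceeds q (1.0, 1.5, 2.0 or 2.5), a look is added at the next time point and charged. With both planned looks the error is 0.050 to 0.053. With one planned look it reaches 0.056.

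**Step 6: access, passages side by side.** G.7 gives interim results to the Project Officer, G.2.1 makes that officer an outcome reviewer, and section F makes the officer a member of the committee that decides the protocol. Section F holds DSMB review results back from investigators until the end, while section H has reports containing interim results prepared together with them. Sections F and H need to be reconciled.

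**The case against.** The strongest reply on error control is that G.3 speaks of planning further looks, which is prospective, and that a decision to stop does not rest on the test alone. Under prospective triggering the inflation is half a point or less in almost every setting tried. This stands as to size. It does not restore the guarantee, because the stated trigger is still the result.

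A reader might infer a larger effect. If every partial analysis is given the boundary of a first look, the error is about 0.063 (O'Brien-Fleming) and 0.076 (0.05t²) at six-monthly intervals. With an opportunity at every 5% of the window it is 0.070 and 0.088. The documents do not support these figures. They discard the two looks that G.3 proposes, and 5% of 40 months is every 2 months, against 6 to 12 in G.1.

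A reader might also take the partial analyses to be unblinded efficacy comparisons. The text does not say so. It is a reasonable inference, since the DSMB reviews efficacy and a pooled result would hardly prompt an efficacy look.

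Nor is the Project Officer shown to be the sole adjudicator or the one who decides the protocol; both roles are shared. Live birth comes from hospital records, so loss classification can hardly move the primary result. Section H covers a joint list of reports and publications and does not say that by-arm results reach investigators, so it shows an ambiguity and no breach. Access rules may also sit in a DSMB charter that is not shown.

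**Conclusion.** The concern holds. As written, G.3 permits effect-driven looks, and alpha spending does not protect the 5% level against them. The size is modest. With the two planned looks kept and every declared look charged, error is about 0.056 to 0.063 under the opportunistic rule. Under the trend rule it is about 0.050 to 0.056, the upper end arising only with a single planned look. These figures rest on triggering rules that I assumed, on the 6-to-12-month schedule, and on partial analyses that show live birth by arm.

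The access gap is real but secondary. It concerns shared authority and unclear wording, and it bears mainly on pregnancy-loss and other secondary outcomes. The documents do not show that the primary endpoint is open to material adjudication bias.

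**What to change.** In G.3, replace the sentence with: *Looks may be added or moved only for reasons unrelated to the observed treatment difference, and every by-arm comparison of live birth is a formal look that spends alpha.* The DSMB keeps its remit over efficacy, but by-arm live birth in a routine report is then charged. With O'Brien-Fleming spending the early charge is small: cumulative alpha is 0.0017 at t = 0.45 and 0.0077 at t = 0.60.

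In G.7 and section H, and in the DSMB charter, state that by-arm interim results go only to the DSMB and the reporting DCC statistician, and that anyone taking part in outcome review stays masked to them. Reconcile section H with section F on what investigators see before the end.

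The cost is wording only, with no change to sample size, visits or the planned looks. The downside is that the Project Officer, through whom the DSMB reports, loses sight of by-arm interim efficacy results.
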